**Move More**			
	Behavior substitution	It’s a beautiful day today, instead of sitting why not grab your lunch, go out and find a place to enjoy your food.	
	Social support	Invite a colleague to join you for lunch today! You can find a nice place outside to sit and enjoy!	
	Problem-solving or barrier identification	If most of your colleagues are inactive people and you think you have no company, you can encourage them or make new friends who are usually active. Invite someone to an afternoon walk now.	
	Instructions on how to perform the behavior	Getting out to walk in the rain is still a great way to connect and enjoy the outdoors. It’s time to take an umbrella and go out!	
	Providing information on the consequences of PA specific to the individual	If you have an active lifestyle it helps you manage your blood sugar. It’s time to do some outdoor light exercises in your neighbourhood.	
	Prompts or cues	Try now if you like: Walk around your building for a break during lunchtime.	
	Prompting generalization of a target behavior	Can you try to increase your activity time (while you do at work) also when you are at home? It’s the right time to be active now!	
	Goal setting	You can achieve your daily physical activity goal (*[>=VALUE minutes]*) by engaging in short walks in your backyard or nearby park, etc. Try it now!	
	Self-monitoring	Check how much time you spent in physical activities yesterday.	
	Feedback on behavior	Congratulations! You achieved your daily physical activity goal *[>=VALUE minutes]* today. Keep up the good work!	

### Overview of Procedures

Eligible participants who provide their consent will be provided with the iMove app installer and invited to a web-based individual orientation session through the Zoom videoconferencing platform. During the web-based meeting, participants will be assisted in installing the app and informed about how to use the iMove app and SORD device. Weight, height, and other demographic measures (age, gender, marital status, job status, and education level) will be assessed at baseline as well as after intervention.

### Data Collection and Storage

Activity sensor data (sitting, standing, and walking time) and other mobile data (location, weather, and calendar information) will be collected automatically through SORD and iMove and sent to a Deakin University secured server. Participant questionnaire data, including demographics questionnaire and system usability, will be captured digitally using Deakin secured Qualtrics surveys.

### Proximal Outcome

Time spent sitting (T_sit_), standing (T_s_), and walking (T_w_) within 1 hour after sending the push notification are the proximal outcomes.

### Distal Outcome

The distal outcomes of interest are the “average weekly time spent sanding and walking altogether, that is, nonsitting time” and the “average time spent being in the sitting state.” Moreover, we will also assess total sitting, standing, walking, and exercising time.

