### Eligibility Criteria

Eligible participants will be adults with T2D, aged between 35 and 65 years, who own an Android smartphone (version 7.0 or higher) and currently interact or engage with apps, have no limitations (including physical problems and medical complications) to engage in low- and moderate-intensity PA, are able to communicate in English, and can provide informed consent.

Volunteers who use other activity trackers and mobile apps that target PA, highly active people, those diagnosed with T2D less than 3 months ago, and people with psychiatric problems, attention, or memory issues will be excluded. We assume highly active people as those who meet World Health Organization (WHO) recommendation of 10,000 steps per day or 150 minutes of moderate to vigorous PA per week. The International Physical Activity Questionnaire—Short Form will be used to assess activity levels [17]. A 1-week run-in period will assess nonadherence with the activity tracker. Individuals with more than 50% incomplete data will be excluded.

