### Intervention Platform

The intervention comprises a bespoke mobile app (iMove app) [18] and a Bluetooth-enabled wearable sensor (SORD) developed and validated by our research group [19]. iMove is a JITAI that aims to support people to decrease sedentary time (Sit Less) and increase PA (Move More) [20]. It consists of a home tab that illustrates sitting, standing, and walking activities, an activity tab to select activities manually in situations where technical issues exist with the app, a goal setting tab to set sitting and walking goals, a notification history tab to compile previous notification messages, and a profile tab (see Figures 2 and 3). SORD is a bespoke thigh-worn device that connects to the iMove app and measures sitting, standing, lying, and PA (eg, walking) [19].

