### Other Outcome Measures

Other outcome measures include feasibility and acceptability. Feasibility will be assessed with descriptive statistics, including the proportion of missing data and engagement with the app (the average time the app was opened every day). Usability is assessed using the System Usability Scale through a web-based survey at the end of the intervention [25,26].

Noncompliance with the intervention platform (ie, SORD and iMove) will be evaluated by sending reminders and phone calls. In case no data have been gathered at one decision point, an automated text message reminder will be sent to the user. This reminder will be triggered once a day. If the data remain uncollected for the second day, the system will notify the research team, and a human investigator will contact the user to encourage them to use the platform and offer assistance in resolving any problems. Each user will be expected to continue the study until they provide data for the corresponding number of days × decision times (42 days × 5 = 210).

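### The distal sitting and nonsitting times are absolute times with no scaling to observed sensor time, so both fall with lost coverage when behavior is unchanged

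*Protocol article*

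**What the plan says.** The Distal Outcome section gives two outcomes. One is "average weekly time spent sanding and walking altogether, that is, nonsitting time" (the first activity is evidently a misprint for standing). The other is "average time spent being in the sitting state", for which no period is stated. It adds that "we will also assess total sitting, standing, walking, and exercising time". None of these is expressed per observed hour or as a share of worn time.

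On the source of the minutes, Intervention Platform states that "SORD is a bespoke thigh-worn device that connects to the iMove app and measures sitting, standing, lying, and PA". Data Collection and Storage says that the activity data "will be collected automatically through SORD and iMove and sent to a Deakin University secured server". The app also has "an activity tab to select activities manually in situations where technical issues exist with the app"; this back-up is not described as covering time when the sensor is not worn.

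On incomplete data:
- Primary Analysis expects gaps from Bluetooth transfer and from states that are not recorded. It enters missing minutes of all three states as zero.
- Limitations and Strengths repeats that transfer to the server may leave gaps.
- Other Outcome Measures sets up reminders and keeps each participant in the study "until they provide data for the corresponding number of days × decision times (42 days × 5 = 210").

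**The concern.** An absolute time taken from a wearable sensor mixes two things: how the person behaved, and how much of the person's time was recorded. The plan expects the second to be incomplete and gives no base that separates the two.

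The aim is less sitting and more standing and walking. Lost recording lowers both measured times together, so it looks like the hoped-for result on sitting and the opposite on nonsitting time. A trend over the six weeks, or a difference between participants, would then partly reflect wear and data transfer.

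The safeguards do not close this gap. The reminder is triggered when a decision point yields no data at all, so a partial loss passes unnoticed. The extension rule counts decision points and not worn minutes. It also lets the number of days enrolled differ between participants, which enters any total directly.

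**Working it through.** **The plan's own figures.** 42 × 5 = 210 decision points per participant and 22 × 210 = 4620 overall both reproduce. They count decision points. The article states no figure for the distal outcomes or for expected wear, so the hours below are illustrations.

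**Inputs**
- Sitting share *p* = 0.64 of waking time. The Introduction gives more than 64%, so this is a lower bound.
- Waking window: 13 h a day, 8 AM to 9 PM, the complement of the preset rest period under Intervention. Using it as the recording window is an assumption. Per week: 13 × 7 = 91 h.
- Coverage *c*, the fraction of that window recorded: assumed values.
- Unrecorded time is assumed to have the same activity mix as recorded time, and lying is ignored.

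**Formulas**
- Recorded weekly sitting = *c* × *p* × 91
- Recorded weekly nonsitting = *c* × (1 − *p*) × 91
- Nonsitting share of recorded time = *c*(1 − *p*) / [*cp* + *c*(1 − *p*)] = 1 − *p*, whatever *c* is

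The first two hold if missing minutes enter as zero. They hold equally if only recorded minutes are summed.

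| Coverage (assumed) | Sitting, h/week | Nonsitting, h/week | Change in both | Nonsitting share of recorded time |
|---|---|---|---|---|
| 100% | 58.2 | 32.8 | 0 | 36% |
| 90% | 52.4 | 29.5 | −10% | 36% |
| 80% | 46.6 | 26.2 | −20% | 36% |
| 70% | 40.8 | 22.9 | −30% | 36% |

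**Sensitivity to the window.** With the 12.5 h span of the decision-point table (8 AM to 8:30 PM), the week has 87.5 h. Sitting is 56.0 h and nonsitting 31.5 h at full coverage, and 44.8 h and 25.2 h at 80%. Both again fall by 20%. The percentage depends only on *c*, not on the window or the sitting share.

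**A drift over time.** Suppose coverage falls from 90% to 70% with no change in behavior (assumed). Recorded sitting falls by 58.24 × 0.2 = 11.6 h and nonsitting by 32.76 × 0.2 = 6.6 h a week. Each is a change of 0.7/0.9 − 1 = −22%. Under the same drift, the true nonsitting share would have to rise from 36% to 0.36 × 0.9/0.7 = 46.3% for recorded nonsitting time merely to stay level.

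**The extension rule.** If one decision point in five yields no data (assumed), reaching 210 takes 210 / (5 × 0.8) = 52.5 days instead of 42. The weekly average over those days keeps its 20% shortfall if the rest of the day is lost at the same rate. A total is then summed over more calendar days for that participant than for one who finished in 42. The longer follow-up offsets the loss in a total only if losses come as whole decision points and at the same rate through the rest of the day. Partial losses trigger no extension.

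**The case against.** The strongest reply is that this is silence and not error. Valid-day rules and wear-time scaling are sensor-processing detail that a condensed article may leave to a fuller document, and an average could be taken over valid days. That would decide the matter if the article said nothing on missing minutes. But it states outcomes in absolute time, and the one rule that it does give sets missing minutes to zero. It is fair to add that this rule stands under Primary Analysis and speaks of decision points, so its use for the distal outcomes is inferred. The result does not depend on that inference, because summing only recorded minutes gives the same shortfall.

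Several stronger readings are tempting and are not supported:
- *Both outcomes are weekly totals.* The nonsitting outcome is a weekly average, the sitting outcome has no stated period, and totals are additional measures.
- *Half of the data may be missing during the trial.* The sentence "Individuals with more than 50% incomplete data will be excluded" belongs to the one-week run-in. It sets no tolerated level for the trial weeks.
- *The extension rule guarantees only five one-hour windows a day, 35 of 91 h a week.* The article does not say what makes a decision point complete, and it does not restrict recording to the outcome windows.
- *The distal results cannot show whether people sat less.* The ratio of sitting to nonsitting time remains computable, and a joint fall in both would itself hint at lost recording. The proportion of missing data is a planned feasibility measure. The sections on analysis state no distal success rule.

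Reminders and contact by the research team should also limit losses. How far is unknown.

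**Conclusion.** The concern holds for the distal outcomes as defined. With behavior unchanged, recorded sitting and nonsitting time both fall in exact proportion to lost coverage: 20% at 80% coverage, or 11.6 h and 6.6 h a week on the 13-hour illustration. The proportionality needs only that unrecorded time resembles recorded time. The coverage values and the hours are assumptions, because the article gives no wear distribution, so the actual size in this trial cannot be stated.

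The change should be made but is not critical. The primary aim, the sample size of 22 and the proximal analysis do not rest on these outcomes.

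**What to change.** Redefine sitting and nonsitting time on one common base, in one of two ways:
- as a share of valid (non-missing) sensor time; or
- as minutes per standard waking day, for example state minutes / valid sensor minutes between 8 AM and 9 PM × 780 (13 × 60).

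In either case:
- Average over days that meet a fixed minimum of valid sensor hours, set before the data are examined.
- State the averaging period for sitting, and how lying time, which the sensor also measures, is treated.
- Say that zero imputation does not apply to the distal outcomes.
- Put the additional totals on the same base, so that they do not depend on days enrolled.
- Report observed hours per week beside each result.

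This is a change of definition and should need no new data collection, provided that the stored record distinguishes missing minutes from true zeros. The costs are that low-wear days are dropped and that worn hours are assumed to represent unworn waking hours.

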### Contextual Measures

Contextual factors, including weather and location, will be assessed using embedded smartphone sensors (GPS) and weather application programming interfaces (APIs; eg, OpenWeatherMap).

### Other Outcome Measures

Other outcome measures include feasibility and acceptability. Feasibility will be assessed with descriptive statistics, including the proportion of missing data and engagement with the app (the average time the app was opened every day). Usability is assessed using the System Usability Scale through a web-based survey at the end of the intervention [25,26].

Noncompliance with the intervention platform (ie, SORD and iMove) will be evaluated by sending reminders and phone calls. In case no data have been gathered at one decision point, an automated text message reminder will be sent to the user. This reminder will be triggered once a day. If the data remain uncollected for the second day, the system will notify the research team, and a human investigator will contact the user to encourage them to use the platform and offer assistance in resolving any problems. Each user will be expected to continue the study until they provide data for the corresponding number of days × decision times (42 days × 5 = 210).

### Data Analysis

#### Primary Analysis

Data from the 22 participants who generated 42 days of expected data, totaling 4620 decision points, will be analyzed. The study days will be continued until we reach the required number of days of data for each individual. Moreover, to deal with missing data at various decision points that could result from Bluetooth issues with the transfer of data or any other reasons (eg, activity states not being recorded), we will impute 0 for all missing minutes of sitting, standing, and walking.

MRT data will be analyzed using the weighted and centered least-squares estimator as previously described [27]. Using this analytical method, time-varying covariates can be handled, and the causal effect can be consistently estimated. Statistical analyses will be performed using R software (R Foundation for Statistical Computing) using the geepack R package.

Primary outcome measures include decision point, day, availability, interventions, and proximal change in activity states (ie, within 1 hour after the intervention is delivered). Overall effects of delivering a suggestion compared with not providing a suggestion on the subsequent 1-hour sitting, standing, and walking behaviors will be assessed. Moreover, linear treatment effects for Sit Less and Move More suggestions will evaluate the interaction between suggestion effects (ie, Sit Less or Move More) and decision points.

Statistics including β estimate, 95% CI, and *P* values will be reported for the average proximal effect as well as the multivariate effect (main effect). Sit less, Move More, and no suggestion (ie, control) conditions will be compared.

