### Aims

The primary aim of this study is to assess the effectiveness of theory-based motivational messages for reducing proximal sitting time and increasing proximal standing or walking time (ie, nonsitting time). The secondary aims involve (1) assessing what type of behavioral components (ie, behavior change techniques) are most effective in reducing sitting time and increasing standing and walking time, measured proximally, and (2) determining relevant contextual moderators for reducing sitting time and increasing standing and walking time.

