#### Sample Size

A total of 22 participants are estimated to detect a small proximal treatment effect size of 0.13 for increasing nonsitting time with 80% power at the level of 5% statistical significance. This was based on the assumptions of 5 decision points per day, a constant randomization probability of 0.7, and an expected participant availability of 70% [16].

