### Limitations and Strengths

Due to the data-intensive nature of this study and the reliance on mobile apps for data transfer, heavy data loads may complicate data transfer to the backend server and generate missing instances. Even though multiple troubleshooting steps have been taken to develop iMove, such issues could still occur on certain smartphones with restricted manufacturers’ system mandates. A key strength of this study is the incorporation of standing as a measured outcome. Because the focus of this MRT is on supporting people with T2D transition from sedentary to more overall physical activities, assessing transitional states, that is, standing, seems relevant. Assessing standing time, distinct from sitting and moving time, is expected to provide more robust evidence on how such Sit Less and Move More MRT performs.

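### Setting every missing minute of sitting, standing and walking to 0 in the primary analysis attenuates the proximal effects, and biases them in either direction if data loss differs by randomized option

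*Protocol article*

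**What the plan says.** The proximal outcomes are the minutes spent sitting, standing and walking "within 1 hour after sending the push notification are the proximal outcomes" (Proximal Outcome). The primary comparison is message against no message: "Overall effects of delivering a suggestion compared with not providing a suggestion on the subsequent 1-hour sitting, standing, and walking behaviors will be assessed" (Primary Analysis). The Aims section defines the nonsitting outcome through "increasing proximal standing or walking time (ie, nonsitting time"), and the Sample Size section powers the trial on it, for "a small proximal treatment effect size of 0.13 for increasing nonsitting time with 80% power at the level of 5% statistical significance".

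For missing data, the Primary Analysis section fixes a single rule: "we will impute 0 for all missing minutes of sitting, standing, and walking". It applies to gaps that "could result from Bluetooth issues with the transfer of data or any other reasons (eg, activity states not being recorded"). The same section says of the weighted and centered least-squares method that "the causal effect can be consistently estimated". Limitations and Strengths expects losses to occur: "heavy data loads may complicate data transfer to the backend server and generate missing instances". The article gives no reason for choosing zero and names no alternative analysis.

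**The concern.** Zero is not a neutral value for these outcomes. It is the lowest possible sitting time, which is the most favorable result, and also the lowest possible nonsitting time, which is the least favorable. The Introduction says people with type 2 diabetes are sedentary for more than 64% of waking time, or about 0.64 x 60 = 38 minutes per hour. A lost hour entered as zero therefore removes about 38 minutes of probable sitting and about 22 minutes of probable nonsitting time.

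Two things are at stake. With equal loss in all options, a true effect is understated and some power is lost. With unequal loss, the primary contrast partly measures the difference in data loss, and the target effect is small enough for a modest difference to matter. Centering in the estimator deals with treatment assignment. It does not repair an outcome filled with a wrong value.

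**Working it through.** **Inputs from the article.** 22 participants; 42 x 5 = 210 decision points each; randomization probability 0.7; availability 0.7; standardized effect 0.13; two-sided 5% level; more than 64% of waking time sedentary.

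**Assumptions.** The article gives neither a loss rate nor an SD for minutes per hour. Loss is taken as 10 to 30% and SD as 15 minutes, with 20 as a check. Mean sitting is 38 to 45 min/h, where 38 comes from the 64% figure. Mean nonsitting is the complement, 15 to 22 min/h.

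**1. The planned figure.** The standard microrandomized-trial calculation uses a noncentral F distribution with noncentrality 22 x 210 x 0.7 x 0.7 x 0.3 x 0.13² = 11.48. A constant effect tested with a linear-in-day model (2 and 18 df) gives 80.2% power and N = 22, which reproduces the Sample Size section. A constant-effect test (1 and 20 df) gives 90%. The stated sample size is not in error.

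**2. Equal loss of whole hours.** With fraction m lost and set to zero:

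- effect in minutes = (1-m) x true effect
- variance = (1-m) x SD² + m(1-m) x mean²

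The second variance term is created by the zeros, so the SD does not shrink in step with the effect. At m = 0.2 and SD 15, the effect falls from 0.13 x 15 = 1.95 to 1.56 minutes. The standardized effect becomes:

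- nonsitting, mean 15: 1.56/√(180 + 36) = 0.106
- nonsitting, mean 22: 1.56/√(180 + 77.4) = 0.097
- sitting, mean 38: 1.56/√(180 + 231) = 0.077
- sitting, mean 45: 1.56/√(180 + 324) = 0.069

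Puts these into step 1 (SD 15; power in %; ranges run over the two means). Leaving the hours missing keeps 0.13 and multiplies the noncentrality by (1-m), for example 0.8 x 11.48 = 9.18.

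| Whole hours lost | Nonsitting, 1-df | Sitting, 1-df | Left missing, 1-df | Nonsitting, 2-df | Sitting, 2-df | Left missing, 2-df |
|---|---|---|---|---|---|---|
| 10% | 79-83 | 60-67 | 86 | 67-71 | 47-53 | 76 |
| 20% | 67-75 | 41-48 | 82 | 54-62 | 30-36 | 70 |
| 30% | 56-66 | 29-35 | 77 | 43-52 | 21-26 | 64 |

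At SD 20 and 20% loss, the nonsitting effect is 2.08/√(320 + 36) = 0.110 to 2.08/√(320 + 77.4) = 0.104. Power is then about 73 to 78% (1-df) or 60 to 65% (2-df).

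**3. Equal loss of scattered minutes.** If 20% of minutes drop out at random within hours, effect and SD shrink almost together. In a simulation of sitting (mean 45, SD 15, limited to 0 to 60), the standardized effect stayed at about 0.126 and 1-df power at about 88%. The effect in minutes is still reduced by 20%.

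**4. Unequal loss.** With no true effect, the false contrast is -(m1 - m0) x mean, where m1 is the loss after a message and m0 the loss without one. For 15% against 10%:

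- sitting: -0.05 x 38 = -1.9 to -0.05 x 45 = -2.25 minutes
- nonsitting: -0.05 x 22 = -1.1 to -0.05 x 15 = -0.75 minutes

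Reversing the imbalance reverses both signs. In simulation (mean 38, SD 15), the sitting contrast without loss was -1.81 minutes. It became -3.45 with 15% against 10% loss, and +0.26 with 10% against 15%. Using recorded hours only gave -1.82 in both cases; loss in that simulation did not depend on the activity itself.

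**The case against.** Much can be said against a stronger statement of this point.

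- **A reader might infer that lost data count as intervention success.** The article does not support that. Zeros enter both sides of the comparison. A false reduction in sitting needs more loss after messages, equal loss pulls the effect toward zero, and the opposite imbalance works against the intervention. Lost time does not become nonsitting time either, because standing and walking are also set to zero.
- **A reader might infer that planned power falls from 90% to 41%.** The plan states 80%, and for nonsitting time. The 41% belongs to sitting (mean 45, 1-df test), for which no power is stated. On the powered outcome the loss is smaller.
- **A reader might call zero on all three states impossible.** The sensor also measures lying (Intervention Platform), and exercising time is listed separately (Distal Outcome), so the three states need not fill the hour. Zero is a poor guess for an unrecorded hour, not an impossible one.
- **Nothing shows that loss depends on the randomized option.** The article describes no such mechanism, so the 5-point difference is an illustration. Nor does it state that loss is independent of the option.
- **The plan has safeguards.** Reminders, staff contact, exclusion at run-in for more than 50% incomplete data, and continuation until 210 points are provided should all reduce the number of empty hours.

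These points limit the size and direction that can be claimed, and all of them stand. They do not rescue the rule. The safeguards act before it, and the Primary Analysis section adds zero imputation to the extension of follow-up. Attenuation in minutes needs no assumption about unequal loss.

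**Conclusion.** The rule is wrong as written and sits in the primary analysis, so it should be changed before the data are analyzed. Any nonzero loss reduces a true effect in minutes to (1-m) of its value. The power cost depends on the pattern of loss: slight for scattered minutes, material for whole hours. At 20% whole-hour loss and SD 15, it is about 7 to 15 percentage points (1-df) or 8 to 16 points (2-df) on nonsitting time, compared with leaving those hours missing. For sitting it is larger: 41 to 48% against 82%, or 30 to 36% against 70%.

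If loss differs by option, each 5 percentage points shifts the sitting contrast by about 1.9 to 2.25 minutes, roughly the whole target effect, in either direction. The claim of consistent estimation therefore does not hold for zero-filled outcomes. Under equal loss, a true null effect remains null, so the problem there is understatement and lost power, not a false positive result.

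Confidence in the defect is high. Confidence in its size is limited, because loss rate, loss pattern and SD are all assumed.

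**What to change.** Delete the zero-imputation rule from the primary analysis and replace it as follows.

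- Treat unrecorded minutes as missing.
- Pre-specify the minimum number of recorded minutes for an hour to be analyzed, and base each outcome on recorded time in those hours. The threshold is for the trial team to choose.
- Handle the remaining hours by multiple imputation, or by inverse-probability-of-observation weights in the weighted and centered least-squares model. Predictors could include prior activity, time of day, location, participant and randomized option. Simply omitting these hours is unbiased only if loss is unrelated to the outcome.
- Report missing minutes by randomized option. The article plans only an overall proportion of missing data.
- Keep zero imputation at most as a sensitivity analysis.

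The cost is analysis-plan wording, some programming, and slightly fewer usable decision points. No new data are needed.

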### Intervention

#### Overview

Through the iMove app, participants will receive a series of Sit Less and Move More intervention messages (notifications) to serve as cues to action [21] and increase readiness to engage in activity. A pop-up message will appear on the phone screen with a sound effect when a notification is received. There will be 2 intervention options, which include Sit Less (sedentary interruption and transition to standing) and Move More (walking) for 1.5-3 minutes, approximately equivalent to 500-1000 steps, and a control option (no messages). Participants can switch off the push notification for a certain amount of time on any given day.

A list of messages is provided in Multimedia Appendix 1.

Notifications are adapted to 4 different context dimensions, including time of day, day of the week (weekend vs weekdays), location (home vs workplace), and weather conditions (good or suitable for PA, rainy and cold or not suitable for PA). Notifications are delivered on 5 occasions (decision points) throughout the day and include morning, lunchtime, afternoon 1, afternoon 2, and evening (details are presented in the “Decision Points” section below).

At each decision point, participants are randomized only if they are available (ie, they are not driving, not sleeping, not active already, and are connected to the internet). The following probabilities are used for randomization: 70% in the intervention (35% SB, 35% PA) and 30% as active control at each particular decision point. GPS will assist with the recognition of driving if the user is on the move. A preset time (9 PM to 8 AM) will be considered for rest and sleeping. In addition, both driving and sleeping can be manually modified by users.

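### The primary analysis names geepack for 22 participants but no small-sample correction; if its ordinary output is used, the nominal 5% tests run at about 7%, and higher for joint tests

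*Protocol article*

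**What the plan says.** Under Data Analysis, Primary Analysis, the protocol article selects the weighted and centered least-squares estimator by reference to a cited method paper. It then names the software: "Statistical analyses will be performed using R software (R Foundation for Statistical Computing) using the geepack R package". On reporting it says: "Statistics including β estimate, 95% CI, and *P* values will be reported for the average proximal effect", and for a multivariate (main) effect as well. The section also plans a comparison of Sit Less, Move More and no message, and an interaction of each message type with decision point.

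Under Sample Size: "A total of 22 participants are estimated to detect a small proximal treatment effect size of 0.13", "with 80% power at the level of 5% statistical significance".

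Neither section names a standard-error option, a test statistic, a reference distribution or a small-sample adjustment.

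**The concern.** In a microrandomized trial, inference for this estimator rests on a sandwich variance summed over people. The information for that variance comes from 22 independent clusters, however many decision points each contributes. Two things go wrong with so few clusters if nothing is done:

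- The uncorrected sandwich is biased downwards, because fitted residuals are smaller than the true errors.
- A normal or chi-square reference ignores the uncertainty in the variance estimate.

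Both make P values too small and CIs too short, and the effect grows with the number of treatment terms tested together. geepack's ordinary output has both features. At stake is the 5% level on which the sample size rests, above all for the option-specific and interaction results that are meant to show which components work.

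**Working it through.** **Inputs from the article.** 22 participants; 42 days × 5 = 210 decision points each, 4620 in total; "5 decision points per day, a constant randomization probability of 0.7, and an expected participant availability of 70" per cent; standardised effect 0.13; 80% power; 5% level (taken as two-sided); allocation "70% in the intervention (35% SB, 35% PA) and 30% as active control at each particular decision point".

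**Step 1: the article's own sample size.** Standard formula for this design with a constant effect: noncentrality λ = N × T × τ × ρ(1−ρ) × d².

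λ = 22 × 210 × 0.7 × (0.7 × 0.3) × 0.13² = 11.48.

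| Treatment-effect model (assumed) | Reference | N for 80% power | Power at 22 |
|---|---|---|---|
| Intercept only | F | 18 | 89-90% |
| Intercept only | chi-square | 16 | 92.3% |
| Intercept + linear day trend (p = 2; q = 1 or 2) | F(p, N−q−p) | 22 | 80.5% or 80.2% |
| Intercept + linear day trend | chi-square | 19 | 86.8% |
| Quadratic | F | 26 | 71-72% |
| Quadratic | chi-square | 21 | 82.2% |

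Here p counts treatment-effect terms and q control terms. The stated 22 is reproduced with a small-sample F reference under a linear-trend model. The article does not state that model, and the quadratic chi-square variant comes within one participant, so this shows compatibility and no more.

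**Step 2: rough size of the problem for one coefficient.** Suppose the variance is too small by (n−1)/n and the statistic truly follows t with 19 df (22 minus 3 parameters). Using 1.96 then amounts to a cut-off of 1.96 × √(21/22) = 1.915, and P(|t₁₉| > 1.915) ≈ 0.071. The reference distribution alone gives P(|t₁₉| > 1.96) = 0.065. So about 7% is expected before any simulation.

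**Step 3: simulation under no effect.** 22 people, 210 points each, about 70% availability, centered treatment terms, person-level sandwich. Autocorrelation, person effects and between-person variation in availability are assumed, since the article gives none. The ranges cover three sets of simulations with different assumptions. For 3,000 trials the Monte Carlo error at 7% is 1.96 × √(0.07 × 0.93/3000) = 0.9 points.

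| Test at nominal 5% | Uncorrected sandwich, chi-square | Mancl-DeRouen with t/F reference |
|---|---|---|
| Any message vs none (1 df) | 6.9-7.7% | 3.8-4.8% |
| Each option vs none (1 df) | 6.4-8.0% | not run |
| Intercept + day trend (2 df) | 8.0% | 3.2% |
| Sit Less and Move More jointly (2 df) | 7.6-10.2% | 2.9-4.7% |
| Joint with linear interaction (4 df) | 15.3-16.6% | 2.9% |

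The first row corresponds to about 93% coverage for a nominal 95% CI. A simpler correction, n/(n−1) with t on 19 df, gave 5.2-5.5% for any message versus none. Mancl-DeRouen with the chi-square reference kept gave 5.7-6.3% for that test, 7.2-7.3% for the two-option joint test and 11.7% for the 4-df test. Both the variance and the reference therefore have to change.

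**Step 4: cost in CI width.** Simple correction: (2.093/1.96) × √(22/21) = 1.093, about 9% wider. Mancl-DeRouen with t, by simulation: about 13% wider.

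**The case against.** A reader might infer that the planned P values and CIs are wrong as they stand. The article does not support that. It names a package, not a function, a standard-error option or a test, and a corrected variance can be computed from a geepack fit. The estimator is taken from a cited paper that may carry its own small-sample correction. The choice of variance estimator is also a detail that a condensed article may leave to the full analysis plan. And 22 can be reproduced with an F reference, which fits planners who had few clusters in mind. All of this stands, and it makes the point conditional.

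A reader might also take the 15-16% figure as the error rate of a planned test. The article mentions a multivariate effect, a comparison of three conditions and interactions with decision point, but specifies no joint 4-df hypothesis. That figure shows only how the problem grows with the number of terms.

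Finally, the excess for the overall effect is modest, about 2 to 3 percentage points, and the recommended correction overshoots slightly. That is also right.

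What remains is that the article does fix the estimator, the software and the reported quantities for 22 people, and that following it literally with the package's ordinary output would not hold the stated 5%.

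**Conclusion.** The point holds in conditional and moderate form. If uncorrected sandwich errors and Wald chi-square tests are used, the nominal 5% level becomes about 7% for any message versus none and for each option, and about 8-10% for a joint test of Sit Less and Move More. Joint tests that include interactions would be worse.

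The direction follows from having 22 clusters. The exact sizes rest on assumed within-person correlation, person effects and availability patterns. Whether the problem will arise depends on the cited method and any fuller plan, neither of which is shown.

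**What to change.** Keep weighted and centered least squares and the geepack fit. Add one sentence to the plan: CIs and P values come from a small-sample corrected person-level sandwich (for example Mancl-DeRouen), with a t reference for single coefficients and an F reference for joint tests, on 22 minus the number of model parameters as degrees of freedom (fewer if fewer people are analysed). If the cited method already includes such a correction, say so. State it before the data are analysed, so that nobody chooses between two sets of P values afterwards.

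The cost is a few lines of code, CIs about 9-13% wider, and tests that run slightly below 5% (about 3-5% in the simulations). N need not change, because 22 can be reproduced with a small-sample F reference under the assumed linear-trend model.

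Adjusting for nonsitting time in the hour before each decision point, which SORD records, is an optional gain in precision. It is a separate matter and does not cure this problem.
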